#### Interim Analyses and Stopping Rules

No interim analysis was performed. However, in the event of disruptive events such as conflict, natural disaster, implementation of similar interventions in the study area, or the deteriorating health and humanitarian situation, we will assess the implications of the study design, stop the study if necessary, and assess the implications on the feasibility of the design to produce evidence on the implementation and effectiveness of the intervention.

## Results

The trial is completed. The recruitment began on July 15, 2019, and data collection began on July 23, 2019, and was completed in November 2020. Data cleaning or analyses began at the time of submission of the protocol. As the randomization is performed at the health facility level, we will undertake aggregate cluster-level analysis comparing the proportion between treatment arms [30]. We will compare differences in the proportion of perinatal mortality between intervention and control groups using a chi-square statistic adjusted for the effect of clustering within health facilities [31] using a formula that incorporates the intraclass correlation coefficient as a measure of the extent of clustering [32].

The analysis and report of the intervention effect will be carried out in accordance with CONSORT (Consolidated Standards of Reporting Trials) principles and its extension for pragmatic trials [33].

We will perform all analyses using Stata version 16.1 software (Stata Corp).

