### Primary Outcome

The perinatal mortality rate per 1000 live births occurring in each facility and the corresponding catchment area for the births that had taken place in the facility will be used to assess the effectiveness of the intervention. It is defined as the sum of *fetal deaths* (stillbirth), defined as the death of a fetus weighing 500 g or more, or of 22 weeks of gestation or more, occurring in health facilities, and *early neonatal death*, namely, the death of a live born within the first 7 days of life occurring in the facility or in the community. As health facility studies are not an appropriate source of data for calculating perinatal mortality incidence [24] unless all babies are born and stayed in a health facility for 7 days, the data on perinatal mortality will be extracted from both facility-level data and household survey questionnaires.

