### Sample Size

A sample size of 600 births per cluster was calculated to have 80% power to detect a reduction in the perinatal mortality rate from 30% to 27% live births, which corresponds to a 10% reduction in the perinatal mortality rate between intervention and control arms (α=5%, intracluster correlation of 0.003, and coefficient of variation of cluster size 0.9 and a 0.96 correlation of baseline measures with outcome). The number of clusters available per arm was 28. The expected average number of deliveries per month in each cluster was approximately 38, resulting in 16 months of follow-up. Two additional months of data collection are planned to account for losses and refusals and allow for adjustments in the analysis, resulting in a final average cluster size of approximately 675 births over 18 months.

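### The primary test is ambiguous between a cluster-level analysis with no stated weighting and an ICC-adjusted chi-square, and the only named test lacks the baseline adjustment on which the stated power depends

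*Protocol article*

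**What the plan says.** The primary analysis is described in two consecutive sentences of the Results section of the protocol article. Because randomisation is by facility, "we will undertake aggregate cluster-level analysis comparing the proportion between treatment arms". The next sentence says that perinatal mortality proportions will be compared between intervention and control "using a chi-square statistic adjusted for the effect of clustering within health facilities", through a formula that uses the intraclass correlation. The first sentence gives a level of analysis but no test and no weights. The second gives the only named test. Neither mentions a baseline measure.

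The Sample Size section claims "80% power to detect a reduction in the perinatal mortality rate from 30% to 27% live births" with 28 clusters per arm and 600 births per cluster. Its inputs are "α=5%, intracluster correlation of 0.003", "coefficient of variation of cluster size 0.9" and "a 0.96 correlation of baseline measures with outcome". The Primary Outcome section puts the outcome on another scale: "The perinatal mortality rate per 1000 live births occurring in each facility".

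**The concern.** In standard usage the two sentences describe different calculations. A cluster-level analysis treats each facility's proportion as one observation and needs no ICC formula. An ICC-adjusted chi-square compares proportions pooled over births and inflates the variance with the ICC. When facilities are of similar size the two nearly coincide. When sizes vary as much as the plan assumes, the weight given to small and large facilities differs sharply, and one test can be significant while the other is not. Someone holding the data could defend either from the text. According to the Results section the trial is complete, and cleaning or analysis had begun at submission.

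The second problem is one of consistency. The sample size takes a large gain from a baseline measure, but the test named for the primary outcome makes no use of one. An analysis without the baseline term would not have the power on which the trial was sized.

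**Working it through.** **Step 1. Reproduce the stated power.** Inputs from the Sample Size section: k = 28 per arm, m = 600, ICC = 0.003, CV = 0.9, r = 0.96, alpha 0.05. Sidedness is not stated; I take two-sided.

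- Design effect: 1 + ((CV² + 1)m − 1) × ICC = 1 + (1.81 × 600 − 1) × 0.003 = 4.255.
- Effective births per arm without baseline: 28 × 600 / 4.255 = 3,948.
- With baseline: 1 − r² = 1 − 0.9216 = 0.0784, so 3,948 / 0.0784 ≈ 50,360.

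Power = Φ(|p1 − p2| / SE − 1.96), with SE² = [p1(1 − p1) + p2(1 − p2)] / effective n.

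| Rates | With 0.96 correlation | Without |
|---|---|---|
| 30 to 27 per 1000 | SE 0.00105, power 81.6% | SE 0.00375, power 12.3% |
| 30% to 27% as printed | above 99% | 84.0% |

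The per-1000 reading with the baseline factor comes within 2 points of the stated 80%, uses every listed input, and matches the scale of the primary outcome. I use it from here on.

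**Step 2. Write out the two tests.**

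- Cluster-level, simplest form: a two-sample t-test on the 28 + 28 facility proportions, equal weights.
- Adjusted chi-square (Donner-Klar): X² = Σ Nᵢ(Pᵢ − P)² / [Cᵢ P(1 − P)] on 1 df, where Cᵢ = Σⱼ nᵢⱼ[1 + (nᵢⱼ − 1)ICC] / Nᵢ and the ICC is estimated by analysis of variance.

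**Step 3. Simulate with no effect.** Beta-binomial outcomes, 28 against 28 facilities, mean size 600, CV 0.9, ICC 0.003, no baseline term (neither sentence has one). Size is unrelated to risk, so the true difference is zero under any weighting. The main runs used gamma sizes and 40,000 replicates, at rates of 0.03 and 0.30.

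| Quantity | Result |
|---|---|
| Unweighted t-test rejects | 4.7-5.0% |
| Adjusted chi-square rejects | 5.9-6.1% |
| The two disagree | 7.4-7.8% |
| Either rejects | 9.0% (rate 0.30) to 9.4% (rate 0.03) |

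Sensitivity runs (8,000 replicates each):

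- Gamma or lognormal sizes, rate 0.03 or 0.30, ICC estimated or fixed at 0.003: either rejects in 8.1-9.2%.
- Mean size 675 (Sample Size section), or 357 (the Abstract's 30,000 newborns over 84 facilities): 9.0%.
- CV 0.3 in place of 0.9: 6.2%. The unequal sizes drive the result.

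The weighting of the cluster-level analysis also matters (40,000 replicates). With weights n/(1+(n−1)ICC) it rejects in 5.3-5.5% alone, disagrees with the chi-square in 4.0-4.1%, and either rejects in 7.6-7.8%. Weighted by births with an ordinary weighted-regression standard error, it rejects in 10.8-11.0% on its own, so that form is not a valid test here.

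**Step 4. Precision.** In 6,000-run simulations (gamma / lognormal sizes, rate 0.03), the standard deviation of the estimated difference was 0.0038 / 0.0038 pooled over births, 0.0041 / 0.0036 with equal weights, and 0.0034 / 0.0034 with weights n/(1+(n−1)ICC). The weighted estimate is about 10% more precise than the pooled one and 5-17% more precise than the equally weighted one.

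**The case against.** The strongest reply is that the protocol names only one test. The first sentence explains why the analysis respects facilities, and the second says how. No t-test, no equal weighting and no choice between methods is offered, so the conflict depends on a test that the reader supplies. This reply largely stands as to emphasis: the text is ambiguous, and it does not declare two competing primary analyses. It does not remove the point. If the chi-square is the whole analysis, the cluster-level label is wrong for it, and the named test still lacks the baseline term.

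A reader might infer that the two sentences target different quantities, a facility-average rate and a birth-average rate. The documents do not support that. It needs equal facility weights, which are nowhere stated; a birth-weighted cluster-level analysis targets the same difference as the pooled comparison. In the simulation both targets are zero, so the excess reflects weighting alone.

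A reader might also take 9% as the trial's actual error rate. It is a worst case per comparison: it supposes that both tests stay open and the smaller p-value is always used. About 1 point of it is the chi-square's own small-sample inflation.

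The Blinding section says that the primary analysis will be blinded to intervention status. That limits choosing a test by the direction of effect. It does not stop a choice by p-value.

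Weights and interval methods are often left to an analysis plan, and their absence alone is no fault. Nor does a chi-square preclude an effect estimate: the same paragraph speaks of differences in proportions and of reporting the intervention effect. The point rests on what is stated: two sentences that do not fit together, and a named test that does not fit the sample size.

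Finally, if 30% to 27% were meant literally, power without baseline would be 84.0% and the mismatch would disappear. That reading conflicts with the per-1000 outcome and makes the 0.96 correlation superfluous.

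**Conclusion.** The point holds in two parts.

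1. The primary test is ambiguous as written. At the plan's CV of 0.9 the plausible readings would disagree in about 4-8% of trials with no effect, depending on the weights. Leaving both open would give a per-comparison false-positive rate of about 8-9% at worst, against 5-6% for either test alone.
2. The named test does not match the sample-size basis. Power is about 82% with the 0.96 correlation and about 12% without it. This assumes rates of 30 to 27 per 1000, two-sided 5%, and the correlation applied as 1 − r² to the whole variance.

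The 82% is the plan's own arithmetic and no guarantee of what adjustment will deliver. If 0.96 describes the stability of true facility rates, sampling error lowers the correlation of observed proportions at 600 births to 0.96 × 600 × 0.003 / (1 + 599 × 0.003) = 0.62, and power to about 17%. The documents do not say which is meant.

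This should be corrected, but it does not by itself invalidate the trial.

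**What to change.** Name one primary analysis before any comparison by arm: a cluster-level regression of the facility perinatal mortality proportion on arm, weighted by n/(1+(n−1)ICC), adjusted for the facility baseline measure that the Sample Size section assumes, with t-based confidence intervals. Keep the adjusted chi-square as a sensitivity analysis only. State in the Sample Size section which baseline measure the 0.96 refers to, and put the rates on the per-1000 scale if that is what was meant.

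The documents describe a December 2016 facility assessment used for eligibility, but they do not say that it recorded facility mortality. If no facility baseline rate is available, keep the weighted analysis and restate the power without the 0.96 correlation.

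The cost is revised wording and slightly more analysis work, with no new data if the assumed baseline measure exists. One downside should be stated openly: these weights are neither purely per birth nor purely per facility, so the report must say what average the estimate represents.

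### The stated 80% power rests on a 0.96 baseline correlation that the named primary test does not use; with rates read per 1000, that test has about 13% power, and 0.96 itself needs justification

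*Protocol article*

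**What the plan says.** The Sample Size section of the protocol article claims "80% power to detect a reduction in the perinatal mortality rate from 30% to 27% live births". The inputs it lists are a 5% significance level and "intracluster correlation of 0.003, and coefficient of variation of cluster size 0.9 and a 0.96 correlation of baseline measures with outcome", with 28 clusters available per arm. It then adds two months of data collection, "resulting in a final average cluster size of approximately 675 births over 18 months", partly to leave room for unspecified adjustments.

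The Primary Outcome section puts the endpoint on a different scale from the printed percentages: "The perinatal mortality rate per 1000 live births occurring in each facility".

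The Results section names the primary comparison. It is an aggregate cluster-level comparison of proportions, made "using a chi-square statistic adjusted for the effect of clustering within health facilities [31] using a formula that incorporates the intraclass correlation coefficient". Neither a baseline covariate nor a change score is mentioned there.

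**The concern.** A baseline-outcome correlation reduces the variance only in an analysis that conditions on baseline. The sample size takes a very large credit of this kind, since 1 − 0.96² = 0.078. The named test adjusts for clustering through the ICC and for nothing else. The power statement and the primary test therefore describe two different analyses.

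At stake is how the result is interpreted. The trial is meant to inform decisions on replication and scale-up. If the test is run as described, a real 10% reduction would usually be missed, yet the non-significant result would stand beside a claim of 80% power.

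**Working it through.** **Inputs.** From Sample Size: 28 clusters per arm, m = 600 births per cluster, ICC = 0.003, CV of cluster size = 0.9, r = 0.96, α = 5%. Assumptions: α is two-sided (the article does not say), and the rates are 0.030 and 0.027 (checked in step 3).

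**1. Reproduce the plan's 80%.** The article prints no formula. I used the usual design effect for unequal cluster sizes and the usual factor for baseline adjustment.

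- Design effect = 1 + [(1 + CV²)m − 1] × ICC = 1 + (1.81 × 600 − 1) × 0.003 = 4.255
- Baseline factor = 1 − r² = 1 − 0.96² = 0.0784
- Variance without baseline = (0.030 × 0.970 + 0.027 × 0.973) × 4.255 / (28 × 600), so SE = 0.003745
- SE with baseline = 0.003745 × √0.0784 = 0.001049
- z = 0.003 / 0.001049 = 2.86, so power = **81.6%** (80.2% with a t reference on 54 df)

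This matches the stated figure.

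**2. Power of the test in Results.** Removing the baseline factor gives z = 0.003 / 0.003745 = 0.80 and power = **12.6%**, counting both tails (12.3% in the direction of benefit).

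| Variation, r = 0 | Power |
|---|---|
| 675 births per cluster | 12.8% |
| 357 births per cluster (30,000 / 84, from the Abstract) | 11.5% |
| Both intervention arms pooled against control | about 15% to 16% |
| One-sided 5% | 19.9% |
| No clustering at all | 37.9% |

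The last row shows that the 80% rests wholly on the baseline correlation. About r = 0.958 is needed to reach it. Without baseline, 80% power at 600 births per cluster would take about 342 clusters per arm. The reduction that the stated test detects with 80% power is from 30 to about 20.1 per 1000, which is 9.9 / 30 = 33%.

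**3. Units.** With the rates taken literally as 0.30 and 0.27:

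- r = 0.96: power is about 100%, and about 10 births per cluster would suffice for 80%
- r = 0: SE = √[(0.30 × 0.70 + 0.27 × 0.73) × 4.255 / 16,800] = 0.01015, z = 2.95, power about 84%

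The literal reading therefore cannot be the calculation that led to 600 births at 80% power. The per-1000 reading reproduces that figure and agrees with the Primary Outcome section.

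**4. Can r = 0.96 be reached?** Suppose facility effects are perfectly stable over time and the baseline period is as large as the trial period. The correlation between two cluster rates is then m × ICC / [1 + (m − 1) × ICC].

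- m = 600: 1.8 / 2.797 = 0.64
- Size-weighted m = 1.81 × 600 = 1086: 3.258 / 4.255 = 0.77

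At m = 600, r = 0.64 gives 18.1% power and r = 0.77 gives 24.1%.

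**The case against.** **Printed units.** Read literally, the percentages give the unadjusted test about 84% power and the shortfall disappears. The arithmetic is right, so the 13% must be stated as conditional on the per-1000 reading. That reading is still the better one, because the literal figures cannot produce the plan's own sample size.

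**Analysis plan not shown.** The article is condensed, and a separate plan may include baseline adjustment. Sample Size does mention room for adjustments. A reader might infer that no baseline mortality was measured or that no adjusted analysis exists. The documents do not support that: the content of the December 2016 facility assessment is not described, and registers are read retrospectively, so pre-trial data may be obtainable. What stands is narrower. The article itself names a test and a power, and they do not match.

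**Where the fault lies.** A reader might infer that swapping the chi-square for a baseline-adjusted model would restore 80% power. The plan's own ICC and cluster size do not support this, as step 4 shows. Most of the shortfall comes from the assumed 0.96 and only a small part from the choice of test.

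**Consequences.** That a null result would be taken as proof that the training fails is conjecture. The documents show only that such a result would be reported beside a power figure that does not apply to it.

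**Conclusion.** The point holds in this form: the 80% power in Sample Size does not describe the primary test in Results. With the rates read as 30 and 27 per 1000, that test has about 13% power for the targeted 10% reduction and reaches 80% only for a reduction of about 33%. The conclusion rests on the per-1000 reading, a two-sided 5% level and pairwise comparison of 28 against 28 clusters. Across the per-1000 variations in the table, the clustered test never exceeds about 20%. The printed percentages are a separate unit error. The 0.96 is unsupported whichever test is used: the plan's inputs point to 0.64 to 0.77 at most with an equal-sized baseline, and so to about 18% to 24% power even after adjustment.

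**What to change.** 1. **Sample Size.** Correct the unit to per 1000 and restate power for the analysis actually planned. For the chi-square as written, that is about 13% for a 10% reduction and 80% for about a 33% reduction. For an adjusted analysis, give the power at a justified baseline correlation. Do not keep 0.96 without showing its source and how it fits with the ICC of 0.003.

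2. **Results.** If facility-level perinatal mortality before the trial can be obtained from the registers, make a baseline-adjusted cluster-level analysis primary, specified before unblinding, and keep the chi-square as a sensitivity analysis. State that register-only baselines miss community deaths, which the Primary Outcome section gives as its reason for household surveys, and that they may therefore correlate less with the outcome. Adjusting for district or delivery volume is optional and not part of this error.

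The cost is a less favourable stated power and, if not already held, extraction of pre-trial register totals for 84 facilities. Trial conduct is unaffected. The Blinding section says that the primary analysis is blinded to facility status, but the article also says that data cleaning or analyses had begun. Whether the change can still precede unblinding must be confirmed. The power statement can be corrected in either case.

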## Discussion

### Study Dissemination Strategy

This operational research study aims to improve the practical knowledge of health workers to improve the quality of management of childbirth and PNC to reduce perinatal mortality. It is part of Mali’s ongoing efforts to achieve target 3 of the Sustainable Development Goals and whose results would be useful for potential replication or scale-up. We will valorize the findings by adopting strategies for dissemination and knowledge transfer. For this purpose, the results will be disseminated to the Ministry of Health and Health Care providers. We will also hold a deliberative workshop with project users and stakeholders to discuss the results and lessons learned from the implementation and effects of the intervention to provide guidance from the perspective of replication or scaling-up. In addition, we will disseminate the results among the scientific and political communities through publications in scientific journals and presentations at international conferences.

### Strengths of the Study

The distinctive feature of this intervention compared with the other LDHF interventions is that it adopts problem-based learning, including supervision and audits with feedback [14]. Thus, the audit component will identify knowledge gaps related to the maternal and neonatal care provided in the facilities and then identify the appropriate training modalities to correct deficiencies in the management of maternal and neonatal care around the delivery and in the postpartum period.

The analytical approaches will provide evidence about the benefits and costs of this pragmatic intervention to improve the quality of maternal and newborn care in Mali with the aim of reducing perinatal mortality. The results will provide policy makers and practitioners with crucial information to facilitate the translation of best practices in capacity strengthening for health care providers in the routine practice of maternal and child care services. Indeed, although LDHF hands-on training has been implemented and evaluated in some resource-limited settings with the aim of reducing maternal and perinatal mortality, previous studies have analyzed only a few outcomes [17,21].

Another distinctive feature of this trial is that it adopts a pragmatic and holistic approach, and the analysis will contain both qualitative and quantitative data collected over a period of 14 months. The trial will provide a better understanding of how LDHF hands-on training of health care providers and community health workers could complement routine care to improve maternal and child health outcomes in resource-limited settings. In addition, this trial occurs during routine health service delivery and will demonstrate the potential of routinely collecting health management information system data to analyze the effectiveness of a major public health intervention.

### Limitations of the Study

Despite these strengths, some limitations of this study need to be considered. The facility-level data collection instrument was developed based on existing consultation and delivery registries, as well as partograph forms. As data are not being collected by direct observation of health care providers but rather from the partographs and registries they fill out, we are also concerned with the completeness, reliability, and accuracy of data to be collected. To overcome this important limitation, refresher training on the use of partographs will be held in all health facilities that are part of the trial. This will strengthen the health care providers’ capacity to use the partograph and aim to improve data completeness and quality for this study.

Some data will be lost to follow-up if the newborn’s mothers are referred to higher-level health facilities. However, we estimate that this will be a minimal disruption to the trial, and we will report the number of these cases in our analyses. In addition, underreporting of infant deaths is usually greater for deaths that occur very early in infancy in low-income countries [24]. As the Ministry of Health is a stakeholder in this project, a strategy will be developed in cooperation with the study team to motivate health workers to improve data completeness, reliability, and accuracy. We will also triangulate mortality data collected in the health facility with the mortality data collected in the household surveys to assess the level of completeness and accuracy and to reduce the likelihood of underreporting of perinatal and maternal deaths in the facility. The data collector will also conduct a follow-up home visit, aided by community relays and volunteers, for all facility births to minimize losses to follow-up.

Finally, completeness and accuracy of recall, including age at death, may deteriorate with time and is also related to the skill and cultural sensitivity of the person carrying out the interview [24]. However, as the recall period was relatively short in this trial (<21 days), the risk of recall bias will be reduced.

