**Methods:**

The study is a three-arm cluster randomized controlled trial in the Koulikoro region in Mali. The units of randomization are each of 84 primary care facilities. Each trial arm will include 28 facilities. The facilities in the first intervention arm will receive support in implementing mortality and morbidity audits, followed by one-day LDHF training biweekly, for 6 months. The health workers in the second intervention arm (28 facilities) will receive a refresher course in maternal neonatal and child health (MNCH) for 10 days in a classroom setting, in addition to mortality and morbidity audits and LDHF hands-on training for 6 months. The control arm, also with 28 facilities, will consist solely of the standard MNCH refresher training delivered in a classroom setting. The main outcomes are perinatal deaths in the intervention arms compared with those in the control arm. A final sample of approximately 600 deliveries per cluster was expected for a total of 30,000 newborns over 14 months. Data sources included both routine health records and follow-up household surveys of all women who recently gave birth in the study facility 7 days postdelivery. Data collection tools will capture perinatal deaths, complications, and adverse events, as well as the status of the newborn during the perinatal period. A full economic evaluation will be conducted to determine the incremental cost-effectiveness of each of the case-based focused LDHF hands-on training strategies in comparison to MNCH refresher training in a classroom setting.

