### Data Collection Methods

#### Health Facility Data

All the facilities in the intervention and control clusters will be visited once a month to retrospectively and systematically collect detailed data from partographs and registries for all facility births and any newborn that was not delivered in the facility but was referred to the facility for PNC within the first 7 days following birth.

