#### Household-Level Interviews

The data collectors will also conduct a follow-up home visit (during the monthly health facility data collection visit, described above) to all women who recently gave birth in facilities since their last visit to administer a short questionnaire after at least 7 days postpartum to capture any perinatal death, complications, or adverse events, the status of the newborn during the perinatal period, and the mother’s satisfaction with the health care during the facility delivery.

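### The stated recall period of under 21 days does not fit monthly visits with interviews at 7 or more days, and it is used to discount recall error in the primary outcome

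*Protocol article*

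**What the plan says.** Four places in the protocol article bear on the timing of the household interview.

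- *Health Facility Data* sets the visit frequency: "All the facilities in the intervention and control clusters will be visited once a month".
- *Household-Level Interviews* places the home visit "during the monthly health facility data collection visit, described above". It covers "all women who recently gave birth in facilities since their last visit to administer a short questionnaire after at least 7 days postpartum".
- The *Methods* part of the abstract describes "follow-up household surveys of all women who recently gave birth in the study facility 7 days postdelivery".
- *Limitations of the Study* accepts that recall, including recall of age at death, worsens with time. It then treats the risk as reduced "as the recall period was relatively short in this trial (<21 days"). The same section says home visits are meant to reach every facility birth.

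*Primary Outcome* shows why the interview matters. Early neonatal death is "the death of a live born within the first 7 days of life occurring in the facility or in the community". The section adds that facility data alone are not adequate unless babies stay in the facility for 7 days, so the household questionnaire is used as well.

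**The concern.** A monthly visit combined with a 7-day minimum fixes the range of interview ages, and that range goes well beyond 21 days. The abstract gives a third timing, 7 days after delivery, which the schedule delivers only for births that happen to be exactly that old when the collector arrives.

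The written rule also leaves open what happens to a birth in the last week before a visit. It is too young for that visit, and at the next one it no longer counts as a birth since the last visit. If it is interviewed at the next visit anyway, its recall is the longest of all.

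What is at stake is how deaths outside the facility are classified. An interview several weeks after birth also picks up deaths after the first week. Whether such a death enters the primary outcome then depends on the age at death that the family recalls. The short recall period is one of the reasons the article gives for not worrying about this.

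**Working it through.** **Inputs.** Visit interval T: once a month (*Health Facility Data*), taken as 30.4 days, with 28 to 31 as the range. Minimum interview age: 7 days (*Household-Level Interviews*). Stated recall: under 21 days (*Limitations of the Study*). Deliveries: about 38 per cluster per month (*Sample Size*). Assumption: births are spread evenly over the interval, so age at the visit is uniform on 0 to T.

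**Reproducing the stated figure.** One combination gives 21 as an upper limit: a 28-day cycle, recall counted from day 7, and no rollover, 28 − 7 = 21. Under it, 7/28 = 25% of births have no interview. A stillbirth or first-day death would be up to 28 days old at interview.

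**Case (a): births under 7 days old roll over to the next visit.** All births are covered.
- Interview age runs from 7 to T + 7 = 37.4 days; the median is (7 + 37.4)/2 = 22.2.
- Under 21 days: (21 − 7)/30.4 = 46%.
- At 21 days or later: (37.4 − 21)/30.4 = 16.4/30.4 = 54%.

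**Case (b): no rollover.**
- Interview age runs from 7 to 30.4 days; the mean is (7 + 30.4)/2 = 18.7.
- At 21 days or later: (30.4 − 21)/30.4 = 9.4/30.4 = 31% of all births, or 9.4/23.4 = 40% of those interviewed.
- No 7-day interview: 7/30.4 = 23% of births, or 38 × 7/30.4 = 8.75, about 9 per cluster per month.

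The cases are alternatives. The 54% in (a) is the 31% in (b) plus the 23% that rolls over, so 54% late and 23% missing cannot both apply.

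**Range over T.**

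| T (days) | (a) maximum age | (a) at 21 days or later | (b) maximum age | (b) at 21 days or later, of all births | (b) no interview |
|---|---|---|---|---|---|
| 28 | 35 | 50% | 28 | 7/28 = 25% | 25% |
| 30.4 | 37.4 | 54% | 30.4 | 31% | 23% |
| 31 | 38 | 55% | 31 | 10/31 = 32% | 22.6% |

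**What would make the bound true.** Counted from birth, every interview falls within 21 days only if T ≤ 21 without rollover, or T + 7 ≤ 21, that is T ≤ 14, with rollover. Counted from day 7 at T = 30.4, the maximum is 23.4 days without rollover and 30.4 with it.

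**The case against.** The figure may not be meant as an upper bound. The article is written after data collection ended and uses the past tense, so under 21 days could describe typical recall. In case (b) the mean from birth is 18.7 days. In case (a) the mean counted from day 7 is 22.2 − 7 = 15.2. That possibility stands, but the text calls the figure neither an average nor a count from day 7. In case (a), the one that covers every birth, the mean from birth is 22.2 days.

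Recall is also not the only safeguard. The same section plans to triangulate facility and household mortality and to use community relays and volunteers to support the home visits. Facility records still capture stillbirths and deaths in the facility, and newborns referred back in the first week. This stands, and it narrows the exposure mainly to early neonatal deaths in the community. Triangulation does little for a death that no facility recorded.

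A reader might infer that nearly a quarter of births were never followed up. The documents do not support that. The abstract and the Limitations section both intend full coverage, collectors may have deferred these births or returned for them, and field handling is a detail an article may leave out. A special return visit for last-week births would close the coverage gap. It would not shorten recall for births just after the previous visit, so about 31% would still be interviewed at 21 days or later.

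A reader might also infer that the comparison between arms is biased. The schedule is the same in all arms and no differential mechanism is shown.

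**Conclusion.** The point holds as an inconsistency in the article's account of how the primary outcome was ascertained. Under monthly visits with a 7-day minimum, under 21 days is not an upper bound counted from birth. Nor can it be one, counted from birth or from day 7, together with follow-up of every facility birth at those monthly visits. About 54% of births are interviewed at 21 days or later with rollover. Without it, the figure is about 31% of all births, and about 23% have no 7-day interview. These sizes rest on evenly spread births and visits kept to a monthly cycle; irregular visits would change them.

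What follows is possible misclassification of age at death, and possibly missing 7-day status, for community deaths. The number of primary events affected cannot be derived from the document. Actual loss of births and bias between arms are not shown. The point deserves correction but does not by itself undermine the trial.

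**What to change.** Data collection ended in November 2020, so the visit rule cannot be changed after the fact. The authors should describe what was done and analyse accordingly.

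1. In *Limitations of the Study*, replace the 21-day figure with the observed distribution of days from birth to interview, by arm. Reconcile the abstract's 7-day timing with it.
2. In *Household-Level Interviews*, state how births under 7 days old at a visit were handled: rolled over, revisited or not interviewed.
3. Report by arm the number of live births without known 7-day status, and do not count them as survivors by default.
4. Add a sensitivity analysis of the primary outcome by birth-to-interview interval, for example restricted to births dated within 21 days before the interview visit. Defining the restriction by birth and visit dates keeps it independent of the reported outcome.

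The cost is some wording, one variable derived from dates that should already be held, and one extra analysis. The recall figure will look less favourable. The restricted analysis will be less precise: it keeps about 46% of births in case (a), or 14/23.4 = 60% of those interviewed in case (b).
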